### Initial screening, assessment and follow-up

After providing informed consent, participants are asked standardized questions about their demographic characteristics, socioeconomic status and medical history. Clinical data is extracted from the medical records regarding primary tumor, time of primary diagnosis, surgical operation, physical examination, laboratory testing, gynecological examination and imaging examination (Table 1).

**Table 1 Tab1:** Baseline screening, assessment, and follow-up schedule

	At baseline	Time after surgery								Early withdrawal
		14 days	21 days	28 days	3 months	6 months	12 months	18 months	24 months	
Follow-up time window (days)		±2	±2	±2	±7	±7	±7	±7	±7	
Informed consent	●									
Demographic characteristics	●									
Socioeconomic status	●									
Medical history	●									
Information on tumor clinical evaluation and surgical operation	●									
Physical examination	●									
Blood routine examination	●				●	●	●	●	●	
Blood clotting function	●									
Routine urine test	●				●	●	●	●	●	
Routine stool test	●				●	●	●	●	●	
Blood biochemistry	●				●	●	●	●	●	
Hormone testing^a^	●				●	●	●	●	●	●
Tumor biomarkers^b^	●				●	●	●	●	●	●
Gynecological examination^c^	●				●	●	●	●	●	●
Abdominal/pelvic CT/MRI	●	▲								
Chess X-ray	●					●	●	●	●	●
Randomization	●									
Assessment of residual urine^d^		●	●	●	●	●	●			
Uroflowmetry				●	●					
Urodynamic tests				●						
Anorectal function evaluation				●						
Pelvic floor functional testing				●	●					
EQ-5D^e^					●	●	●		●	
PISQ-12^f^						●	●		●	
PFDI-20^g^					●	●	●		●	
ICIQ/OABss^h^					●	●	●		●	
Adverse events	●				●	●	●	●	●	●

●: Indicates mandatory items

▲: Investigator will decide whether to perform the testi according to clinical signs or clinical evaluation

^a^Hormone testing includes estradiol, progesterone, testosterone, prolactin, follotropin and luteinizing hormone

^b^Tumor biomarkers includes squamous cell carcinoma antigen, CA125, CA199 and carcinoembryonic antigen

^c^Gynecological examination includes Human Papillomavirus and Thinprep Cytological Testing

^d^Residual urine is evaluated by B ultrasound

^e^EQ-5D: European Quality of Life-5 Dimensions

^f^PISQ-12: Prolapse/Urinary Incontinence Sexual Questionnaire short form

^g^PFDI-20: Pelvic Floor Distress Inventory

^h^ICIQ/OABss: International Consultation on Incontinence Questionnaire/Overactive Bladder Symptom Score

All the enrolled subjects will be followed up at 14 days, 21 days, 28 days, 3 months, 6 months, 12 months, 18 months and 24 months after the surgical operation. Residual urine following self-urination is evaluated by B ultrasound at postoperative 14 days, 21 days, 28 days, 3 months, 6 months and 12 months. Uroflowmetry, urodynamic parameter, anorectal function and pelvic floor function are assessed at postoperative 28 days; in addition, uroflowmetry and pelvic floor function are evaluated at 3 months after surgery. Quality of life (QOL) is evaluated by European Quality of Life-5 Dimensions (EQ-5D), Prolapse/Urinary Incontinence Sexual Questionnaire short form (PISQ-12), Pelvic Floor Distress Inventory (PFDI-20) and International Consultation on Incontinence Questionnaire/Overactive Bladder Symptom Score (ICIQ/OABss). All QoL related questionnaires are required to be completed during the follow-up at 3 months, 6 months, 12 months and 24 months after surgery, except PISQ-12 at 3 months. During the follow-up at 3 months, 6 months, 12 months, 18 months and 24 months after surgery, information related with laboratory testing, gynecological examination, chest X-ray and adverse events will be collected and assessed.

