### Intervention

All participants who are assigned to the intervention group will receive TENS treatment on the basis of conventional clinical care. The stimulation treatment starts 7 days (±2 days) after radical hysterectomy. Participants receive TENS treatment twice daily for 14 days (28 treatment sessions), and those patients with residual urine >100 ml at 14 days post-operation will take an additional 7 day stimulation treatment (14 treatment sessions). Patients are placed in a supine decubital position. The electric parameters used in each session are homogeneous: current type: functional electrical stimulation; frequency: 1/4/1 Hz; pulse duration: 270/230/270 μs; time: 30 min; surface electrode: 50*50 MM adhesive electrode; stimulation intensity: maximal level tolerable without pain, usually less than 100 mA. One electrode is placed in the S3 region and the other one is crossed on the skin and fixed at the bladder area.

All subjects who are assigned to the control group will receive only conventional clinical care. With the exception of TENS, intervention and control groups have the same study procedures throughout the entire study. The catheter is removed while residual urine is less than 100 ml at 14 days, 21 days or 28 days after surgery. Catheter removal timing is determined according to the recovery of participants if residual urine is >100 ml at 28 days post-operation.

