## Discussion

Lower urinary tract symptoms (LUTS) are usual complications of radical hysterectomy among cervical cancer patients. Among these symptoms, UR, dysuria, loss of bladder sensory and urinary incontinence are most common [17]. Some patients even need suprapubic cystostomy resulting in poor life quality. As an non-invasive treatment method, TENS has been used to treat pelvic floor disorders including bladder dysfunction and has been proven to be effective [11]. TENS modifies the electric impulses of nerve fibers, promotes blood circulation of pelvic organs, thus might help the recovery of bladder sensitivity and increase the contractility of the bladder detrusor.

But by now only few studies have been carried out using electrical stimulation treatment on cancer patients [14–16]. Among these few studies, a trial conducted by Gianna Mariotti [15] had the highest quality based on RCT design. In this study, 60 patients who underwent radical prostatectomy were prospectively randomised to treatment group and control groups. Patients in the treatment group received electrical stimulation and biofeedback from the 7th day postoperative. The treatment was performed twice a week for 6 weeks, patients were followed up at 1, 2, 3, 4, 5 and 6 months. The results showed that treatment with biofeedback and pelvic floor electrical stimulation had a significant positive impact on the early recovery of urinary continence after radical prostatectomy. A previous study conducted by our research team showed that transcutaneous low frequency electrical stimulation from the 11th day after radical hysterectomy can reduce the residual urine volume and shorten the time of indwelling urinary catheter [16].

No research has mentioned the safety of electrical stimulation on cancer patients except our in vitro study, which indicated that electrical stimulation had no effect on cell proliferation, invasion and immigration capacity [18]. Due to the safety uncertainty of TENS on cancer patients, the trial presented here does not include all cervical cancer patients, those who had a high risk of recurrence and might need further ajuvant chemotherapy and/or radiaotherapy will be excluded. Thus all participants are with early cervical cancer (stage Ia2, Ib1 and IIA1, FIGO stage), no other risk factors differed by pathologic diagnosis.

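### The printed schedule has no adverse-event review at the day 14, 21 and 28 visits, so for participants who do not withdraw the first review comes about 54 to 79 days after the last TENS session

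*Protocol article*

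**What the plan says.** All of these places are in the Protocol article.

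- **Visits.** The section Initial screening, assessment and follow-up lists eight postoperative visits for every enrolled participant, the first three of them on days 14, 21 and 28. These three are therefore study visits for both arms.
- **Adverse events in the text.** In the same section: "During the follow-up at 3 months, 6 months, 12 months, 18 months and 24 months after surgery", several items are gathered, ending with "chest X-ray and adverse events will be collected and assessed". Days 14, 21 and 28 are not named.
- **Adverse events in Table 1.** The row "Adverse events" is filled at baseline, at the five visits from 3 to 24 months and at early withdrawal. It is blank at days 14, 21 and 28. The key to the filled circle reads "Indicates mandatory items".
- **Exposure.** Under Intervention, stimulation begins 7 days (±2) after surgery. "Participants receive TENS treatment twice daily for 14 days (28 treatment sessions"), with 7 further days (14 sessions) if residual urine exceeds 100 ml at day 14.
- **Use of the data.** Adverse events are the eighth secondary endpoint (Study endpoints). Their incidence is compared between groups by chi-square or Fisher's exact test (Statistical analysis).
- **Blinding.** Neither participants nor investigators are blinded (Randomisation and blinding).

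**The concern.** The events that a surface-electrode treatment is most likely to cause would occur while it is being given, and many would resolve soon afterwards. The printed schedule asks about adverse events before treatment starts and then not again until long after it has ended, unless the participant withdraws.

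The comparison at stake is a stated secondary endpoint with its own test. If short-lived events in the stimulation weeks are recorded only from memory at 3 months, the incidence in each arm is measured with error. Because both participants and staff know the allocation, that error need not be equal in the two arms. Urinary infection has little back-up either: the routine urine test in Table 1 is also blank at days 14, 21 and 28.

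**Working it through.** **Inputs**

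- Start of stimulation: day 7 ±2, so day s with s = 5 to 9 (Intervention).
- Basic course 14 days, extension 7 days, two sessions a day (Intervention).
- Visit windows: ±2 days at days 14, 21 and 28; ±7 days at 3 months (Table 1).
- Assumptions: treatment is given on consecutive days, an extension follows the basic course directly, and 3 months means day 90.

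**Step 1: the plan's own session counts.** 14 × 2 = 28 and 7 × 2 = 14; both match the text. A participant has 28 sessions, or 28 + 14 = 42 if extended.

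**Step 2: last treatment day.** Basic course: s + 13. Extended course: s + 20.

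| Start day | Basic course ends | Extended course ends |
|---|---|---|
| 5 | 18 | 25 |
| 7 | 20 | 27 |
| 9 | 22 | 29 |

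**Step 3: which early visits fall within treatment.**

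- Day 14 (window 12 to 16): always. The latest start is day 9 and the earliest end is day 18.
- Day 21 (window 19 to 23): always within an extended course, which ends on day 25 at the earliest. In a basic course, only with a late start or an early visit; otherwise it follows the last session closely.
- Day 28 (window 26 to 30): never within a basic course, which ends by day 22. In an extended course, only if the start is late enough or the visit early enough; otherwise it comes after treatment.

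**Step 4: gap from last session to first scheduled review after baseline.** The 3-month visit falls on day 90 − 7 = 83 to 90 + 7 = 97.

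- Basic course: 83 − 22 = 61 to 97 − 18 = 79 days.
- Extended course: 83 − 29 = 54 to 97 − 25 = 72 days.
- Overall: 54 to 79 days.

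Reading 3 months as day 91 moves the overall range by one day, to 55 to 80.

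**Step 5: text against table.** The two do not conflict over the early visits: the text names none of them and the table leaves all three blank. The same table uses those three columns for residual urine, so the columns are in use and the adverse-event cells are empty.

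**The case against.** The strongest reply is that this is a condensed article. A visit grid shows when adverse events are reviewed; it does not say that events between visits are left out of the next record. Spontaneous, per-session or serious-event reporting may be set out in the full protocol, which is not shown. This reply stands against one inference a reader might draw, that device-related harm will be missed or that the comparison will look falsely reassuring. The document gives no event rate and no rule that discards earlier events, so only possible under-recording is supported. The reply does not dispose of the point, because the article is not silent: it prints a schedule with mandatory marks and leaves these cells empty.

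Four other stronger readings also fail.

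- **That no scheduled route exists during treatment.** Early withdrawal is marked, so a participant who leaves during stimulation has adverse events recorded. The gap concerns those who stay.
- **That all three early visits lie inside the treatment period.** Only day 14 always does (Step 3).
- **That retention would go unrecorded.** Residual urine is measured by ultrasound at days 14, 21 and 28, and catheter removal is tied to those visits. Retention is closely tracked in this window.
- **That the authors neglect the hazard they name.** The Discussion phrase "Due to the safety uncertainty of TENS on cancer patients" follows a laboratory study of tumour-cell behaviour and leads to the exclusion of patients at high risk of recurrence. That worry is mainly oncological, and it is followed up through survival endpoints, tumour markers and examinations to 24 months. It says little about local effects during sessions.

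It is also fair to say that both arms follow the same schedule and that intensity is kept below the pain threshold. The first does not remove the problem, since an identical schedule does not make unblinded recall equal across arms. The second makes pain less likely but does not replace asking about it.

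**Conclusion.** The point holds in a limited form. For participants who do not withdraw, the printed schedule places no adverse-event review between baseline and 3 months. All 28 to 42 sessions fall in that interval, and the first review comes about 54 to 79 days after the last session. Transient events during stimulation may be under-recorded or depend on unblinded recall, which weakens the between-group adverse-event comparison.

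The range rests on day 90 for 3 months and on uninterrupted daily treatment. How many events would be affected cannot be estimated from the document. The primary endpoint, the randomisation and the sample size of 208 are unaffected.

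**What to change.** In Table 1 and in the matching sentence under Initial screening, assessment and follow-up, mark adverse events as mandatory at days 14, 21 and 28 in both arms, each time covering all events since the previous visit. If the full protocol already records adverse events continuously from randomisation, state that in the schedule so that the two agree.

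Report events in the treatment period (randomisation to about day 28) separately, alongside later events. Neither table needs to rank above the other: making the early period the main safety table would be a preference, and the authors' stated oncological concern is about the longer term.

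The cost is one form page at three visits that already take place, plus the amendment wording.

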### Study endpoints

The primary endpoint is improvement rate of urination function. Based on self-urination status and residual urine evaluated by B ultrasound following catheter removal and self-urination, efficacy is classified into three levels: 1) recovery: automatic micturition is achieved by patients with residual urine ≤50 ml; 2) improvement: automatic micturition is achieved by patients with residual urine 50–100 ml; 3) invalid: automatic micturition is not achieved, or automatic micturition is achieved but with residual urine ≥100 ml. Improvement rate is calculated as follows: (the number of recovery participants + the number of improvement participants)/the total number of enrolled participants *100%.

Secondary endpoints are: (1) urodynamic parameter, including maximal uroflowmetry, micturition curve, bladder sensation, detrusor muscle stability, detrusor muscle function of contraction, stress urinary incontinence, urinary retention and lower urinary tract obstruction; (2) urinary incontinence evaluated by 1 h pad test is defined as follows: <1 g continence, 1–10 g mild incontinence, 11-30 g moderate incontinence, 31-50 g severe incontinence, >50 g extremely severe incontinence; (3) anorectal function, including rectal sensation, rectal maximum volume, reflex of rectal anal internal sphincter, reflex of rectal anal external sphincter and balloon expulsion testing; (4) pelvic function, including muscle strength of type I and type II muscle fiber of pelvic muscle, fatigue of pelvic muscle, vaginal dynamic pressure and neural reflex; (5) QOL evaluated by EQ-5D, PISQ-12, PFDI-20 and ICIQ/OABss; (6) overall survival (OS), calculated as the time from initial diagnosis to death from any cause or the date of last follow-up for surviving subjects; (7) disease-free survival (DFS), defined as the period from the date of initial diagnosis to the date of recurrence, metastasis, death due to any cause or the date of last follow-up for surviving subjects; (8) adverse events.

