## Methods and design

### Trial design and setting

The trial is conducted as a clinical, multicentre, randomised controlled trial with balanced randomisation (1:1) to examine the efficacy of transcutaneous electrical stimulation (TENS) treatment on the recovery of urinary function among postoperative patients with early cervical cancer. After class III radical hysterectomy, participants with early cervical cancer (International Federation of Gynecology and Obstetrics [FIGO], stage Ia2, Ib1 and IIA1) will be randomly assigned to an intervention or control group. Participants will be stratified by menopausal status and surgical modality. Subjects will be recruited continuously by oncologists from gynecology departments in nine hospitals of Beijing city: Peking University People’s Hospital; Peking University First Hospital; Peking University Third Hospital; Cancer Institute and Hospital, Chinese Academy of Medical Sciences; Peking University Cancer Hospital & Institute; The General Hospital of the People’s Liberation Army; Beijing Obstetrics and Gynecology Hospital, Capital Medical University; Beijing Chaoyang Hospital, Capital Medical University; and Beijing Hospital. Figure 1 illustrates the flow diagram of the study for both the intervention and control groups.

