#### Exclusion criteria

If one of the following criteria is met, patients will be excluded from the study: (1) participants who received neoadjuvant chemotherapy, radiotherapy or chemoradiotherapy before and after operation; (2) received nerve sparing surgery; (3) urinary system injury during a gynecologic operation; (4) diagnosed with ≥ stage II pelvic organ prolapse before operation; (5) preoperative moderate to severe stress urinary incontinence (pad weight testing ≥10 g); (6) preoperative urinary retention; (7) preoperative serious functional constipation or defecation disorder; and (8) participant’s inability to fully comply with study protocol due to uncontrolled epilepsy, central nervous system diseases or psychosis.

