### Sample size consideration

We expect improvement rate of urination function 70% in the intervention group and 50% in the control group. Based on a difference of 20% between groups on the primary outcome, assuming 10% drop-out rate, a total of 208 participants (at 1:1 ratio, 104 subjects in each group) are required to provide 80% power, with the use of two-sided significance level of 0.05.

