### Statistical analysis

Analyses will be made using SAS statistical software (version 9.3) by a statistician in Peking University Clinical Research Institute. Data will be analyzed according to the “intent-to-treat” principle. A two-sided significance level of 5% will be used for all analyses.

Descriptive statistics will be used to summarize demographic and clinical characteristics of participants randomised to the intervention and control groups. The difference between two groups on demographic characteristics, socioeconomic status, clinical characteristics and follow-up retention rate will compared using t-tests (or Wilcoxon rank sum test) and chi-square test/Fisher’s exact test as appropriate.

Primary outcome (improvement rate of urination function in 1 year) analyses will be carried out by Cochran-Mantel-Haenszel tests taking into center effect.

The difference in urodynamic parameter, anorectal function and pelvic function between intervention and control groups will be determined using t-tests or Wilcoxon rank sum tests as appropriate. The severity of urinary incontinence will be analyzed using the Wilcoxon rank sum test. The differences in QOL (evaluated by EQ-5D, PISQ-12, PFDI-20 and ICIQ/OABss) between intervention and control group will be determined using repeated measure analysis of variance (ANOVA). DFS and OS survival curves will be calculated using the Kaplan-Meier method, and compared using the log-rank test. Cox proportional hazards models will also be used to calculate hazard ratio and 95% confidence interval, with other risk factors (such as cancer stage and tumor localization) as covariates.

The incidence of adverse events between 2 groups will be compared with the chi-square test/Fisher’s exact test. Descriptive statistics will be used to summarize incidence rates of adverse events and serious adverse events.

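### Grading the 1 h pad weight into five bands before a rank test discards information and ties the result to band limits that are not contiguous for fractional grams; ranking the grams is a modest, cheap gain

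*Protocol article*

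**What the plan says.** Under Study endpoints, the second secondary endpoint reads "urinary incontinence evaluated by 1 h pad test is defined as follows", followed by five bands: "<1 g continence, 1–10 g mild incontinence, 11-30 g moderate incontinence, 31-50 g severe incontinence, >50 g extremely severe incontinence". No weighing precision or rounding rule is given.

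Under Statistical analysis, the comparison is: "The severity of urinary incontinence will be analyzed using the Wilcoxon rank sum test". No baseline term is mentioned. The only severity scale that the article defines for this endpoint is the five grades, so the natural reading is that the grades are what is ranked.

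Under Exclusion criteria, item 5 also uses a pad weight: "preoperative moderate to severe stress urinary incontinence (pad weight testing ≥10 g". The duration of that test is not stated.

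Table 1 has no row named for the pad test, at baseline or at follow-up. The abstract (Methods/Design) places screening 5–7 days after the operation.

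**The concern.** A 1 h pad test yields a weight in grams. A Wilcoxon test needs only an ordering, and the grams already supply one, skewed or not. Cutting the weight into five grades first has two effects.

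- Every pair of women in the same grade is tied. Weights of 1 g and 9 g count as equal, although the measurement orders them.
- The result depends on where the grade limits lie, and the printed limits do not meet unless weights are in whole grams.

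In addition, the entry criterion and the endpoint definition put different labels on 10 g.

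At stake is some precision on one secondary endpoint, and a definition that works only under a rounding rule that the article does not state. The endpoint has some weight in the trial's own terms, because the Background names incontinence as the long-term bladder disorder after this surgery.

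**Working it through.** The article gives no figure for this endpoint to reproduce. Its one calculated figure is the sample size of 208. That figure does reproduce (70% v 50%, two-sided 0.05, 80% power, pooled variance: 93 per arm; 93/0.90 = 103.3, rounded up to 104; 2 × 104 = 208), but the pad-test point does not depend on it.

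**1. Do the printed grades cover every weight?** Each weight from 0 to 60 g was classified under the bands in Study endpoints.

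- In 0.1 g steps, the ungraded weights are 10.1–10.9 g and 30.1–30.9 g.
- In whole grams, no weight is ungraded.

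The gaps therefore depend on the recording precision. The lowest class, below 1 g, does not settle this: in whole grams it simply means 0.

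**2. Entry label against endpoint label.**

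| Pad weight | Exclusion criteria, item 5 | Study endpoints |
|---|---|---|
| below 10 g | not excluded | continent or mild |
| 10 g | moderate to severe | mild |
| 10.1–10.9 g | moderate to severe | no grade |
| 11 g | moderate to severe | moderate |

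The direct conflict in labels is at exactly 10 g. From 11 g up to 30 g, and from 31 g, both passages place the weight at moderate or worse.

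**3. What does grading cost the rank test?** A usual approximation, for a small shift on a proportional-odds scale, takes the information in a Wilcoxon test as proportional to 1 − Σp³, where p is the share of women in each tied group, averaged over the arms.

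- Five grades: every occupied grade is a tied group, so the information is 1 − Σp³ over all grades.
- Grams, with weights below 1 g tied as continent: only the continent share p₀ is a tied group, so the information is 1 − p₀³.

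The article gives no pad-weight distribution, so two splits are assumed to show a range.

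| Assumed continent/mild/moderate | Grades: 1 − Σp³ | Grams: 1 − p₀³ | Grams ÷ grades |
|---|---|---|---|
| 60/30/10% | 1 − (0.216 + 0.027 + 0.001) = 0.756 | 1 − 0.216 = 0.784 | 0.784/0.756 = 1.037 |
| 40/45/15% | 1 − (0.064 + 0.091 + 0.003) = 0.8415 | 1 − 0.064 = 0.936 | 0.936/0.8415 = 1.112 |

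The gain is about 4% in the first case and about 11% in the second. Nearly all of it comes from breaking ties within the mild grade. The grams column treats all weights of 1 g or more as distinct. Recording in whole grams would leave some ties, so for these splits the figures are upper values.

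**The case against.** The strongest reply is that nothing here is invalid. A Wilcoxon test on an ordered scale is correct with ties, the grades carry clinical meaning, a rounding rule is a detail that a condensed article may leave to the full protocol, and this is one of eight listed secondary endpoints. All of that stands. It is also possible that the sponsor always meant to rank grams, in which case the fix is only a clarification. What remains is that the endpoint and analysis passages, read together, rank grades when a finer ordering is already measured.

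A reader might infer more, and the documents do not support it:

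- **That women near 10 g are misgraded.** The entry criterion is a preoperative exclusion and assigns no outcome grade. A postoperative 10 g is mild in both arms. The conflict is one of labelling. Nor is it shown that both passages use the same test, since the exclusion states no duration and concerns stress incontinence only.
- **That leakage before surgery is ignored and distorts the comparison.** Stress leakage of 10 g or more is excluded, and what remains is spread by "balanced randomisation (1:1". The unadjusted comparison is not biased between arms. The cost is some precision, and new mild leakage cannot be told apart from leakage already present.
- **That a count of affected women can be given.** Assuming that 10–20% enter with 1 g to under 10 g gives 0.10 × 208 = 20.8 to 0.20 × 208 = 41.6, or about 21 to 42 women. The article supports no such prevalence, and the count also needs every one of these women to stay in the same grade after surgery.
- **That a preoperative weight is available to stratify on.** Table 1 shows no baseline pad test and screening follows surgery. The criterion excludes women known to reach 10 g, which does not show that a weight was recorded for every woman.

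**Conclusion.** The point holds as a modest improvement to a secondary endpoint. Ranking the five grades discards ordering that the pad test already provides, and makes the result depend on limits that do not meet for fractional grams. The efficiency gain from ranking grams is about 4% to 11%. This rests on two assumed splits and on the tie approximation; a different distribution would give a different figure. Separately, the exclusion criteria and the endpoint definition label 10 g differently, which is a clerical inconsistency to reconcile. Which cut is right is not for a statistical review to say. There is no bias between arms.

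**What to change.** 1. In Statistical analysis, state that the Wilcoxon rank sum test is applied to the 1 h pad weight in grams, with all weights below 1 g tied at the lowest rank, because Study endpoints defines them as continence.
2. Keep the five grades for description only. Print contiguous limits, so that each weight belongs to exactly one grade, or state the rounding rule under which the present limits are complete.
3. Reconcile the label for 10 g between Exclusion criteria item 5 and Study endpoints.
4. Stratify by the preoperative pad result (van Elteren test, below 1 g v 1 g to under 10 g) only if the sponsor confirms that this weight was recorded for every woman. If it was not, it cannot be collected after surgery and the unadjusted test should stay.

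The cost is one line in the analysis section and wording in two others. No visit, measurement or participant is added. The downside is that the test result is tied less directly to the clinical grades, so the grade table should be reported beside it.
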